## Methods

This observational pilot study will examine the relationships among velopharyngeal anatomy, surgical procedure choice, and early speech outcomes in infants with cleft palate.

### Ethical Considerations

The study was approved by the Colorado Multiple Institutional Review Board (protocol number 22-1135). A reliance agreement is in place with the University of Wyoming Institutional Review Board. Written informed consent will be obtained from all caregivers prior to enrollment. Additional consent provisions are in place for continued data collection and monitoring of the medical chart up to 18 months of age and the use of participant data in ancillary studies; participants may opt out of follow-up at any time.

### Participants and Recruitment

A total of 30 participants will be recruited from the Children’s Hospital Colorado Cleft Lip and Palate Program (Aurora, Colorado), with an initial enrollment of 39 to account for an anticipated 30% attrition due to MRI motion artifacts, refusal, or missed visits. This sample size was selected based on the pilot nature of this work and use of a single recruitment site; furthermore, the sample size is consistent with prior prospective studies using nonsedated MRI of the velopharynx in children [33,36,37]. This study is considered exploratory to evaluate the relationship among anatomy, surgical selection, and early speech outcomes, as well as to support future larger-scale, multicenter studies. The recruitment site receives 50 to ⁠60 new referrals each year, providing ample opportunities to reach the target sample size over the 3-year funding period. Retention strategies will be used to reduce dropout, including regular personalized reminders, flexible scheduling, and incentives. Participants must be from English-speaking families and have a diagnosis of cleft palate that has not yet been repaired. Infants diagnosed with syndromes prior to 18 months (as reported in their medical chart), those ineligible for MRI (eg, metal implants or severe airway anomalies), or those with other contraindications to standard surgical care will be excluded. Those scheduled for primary palatoplasty after 15 months of age will also be excluded from this analysis.

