## Results

This study was funded in August 2024 by the National Institute on Deafness and Other Communication Disorders (R21DC021799). Recruitment and data collection for this study began in April 2025 and are currently underway. As of April 4, 2026, a total of 8 participants have been enrolled, and data analysis has not begun. It is anticipated that enrollment will be complete and final results will be disseminated by the end of 2027 following completion of data analysis.

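### Enrolling 39 at 30% attrition retains about 27 children, not 30, and the recruitment reassurance does not fit the 8 enrolled in the first year

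*Protocol article*

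**What the plan says.** Under Participants and Recruitment, the protocol article states "A total of 30 participants will be recruited from the Children’s Hospital Colorado Cleft Lip and Palate Program", followed by "with an initial enrollment of 39 to account for an anticipated 30% attrition due to MRI motion artifacts, refusal, or missed visits". The size is not derived from power or precision: "This sample size was selected based on the pilot nature of this work and use of a single recruitment site". The section also points to similar earlier imaging studies and describes the work as exploratory. It cites 50 to 60 new referrals a year, "providing ample opportunities to reach the target sample size over the 3-year funding period".

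The Results section gives the dates and the progress so far:
- Funding dates from August 2024, and recruitment opened in April 2025.
- On progress, the section reports: "As of April 4, 2026, a total of 8 participants have been enrolled, and data analysis has not begun".
- Completed enrolment and published findings are both expected before 2028.

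Under Study Design and Data Collection, the presurgical scan is placed at about 10 to 12 months of age and the second scan at about 18 months. No section revises the target, the attrition or the timeline in light of the 8 enrolled.

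**The concern.** There are two separate problems.

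**Attrition.** Enrolling more children to allow for loss only makes sense if 30 is the number to be kept. A loss of 30% is a share of those who enrol, so the enrolment target should come from dividing by 0.70. The stated 39 comes from multiplying by 1.30. The sentence that defines the sample size therefore promises a number that its own attrition rate does not deliver.

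**Accrual.** The article reassures the reader about recruitment and, in another section, reports a first-year count well below the pace needed. Anyone judging how many children will inform each aim has no projection to work from. Aim 2 is the more exposed, because it needs each child to reach the 18-month visit.

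**Working it through.** **Part 1: attrition**

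Inputs from Participants and Recruitment: target 30, enrolment 39, attrition 30%.

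- The plan's figure is reproduced by 30 × (1 + 0.30) = 39.
- Children retained from 39 at 30% loss: 39 × (1 − 0.30) = 27.3, about 27.
- Enrolment needed to retain 30: 30 / (1 − 0.30) = 42.9, so 43. Check: 43 × 0.70 = 30.1.
- Attrition at which 39 yields 30: 1 − 30/39 = 23.1%.

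The shortfall is about 3 of 30 children, or 10%.

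**Part 2: accrual**

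Inputs from Results: recruitment began in April 2025 (day not given, so 1 to 30 April), and 8 were enrolled by 4 April 2026. That is 11.1 to 12.1 months.

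- Observed rate: 8 / 12.1 = 0.66 to 8 / 11.1 = 0.72 per month.
- Still needed for 39: 39 − 8 = 31.
- Projected total = 8 + rate × months remaining from 4 April 2026.
- Required rate = 31 / months remaining.

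The article gives no last-enrolment date, so each deadline below is an assumption. Three years from August 2024 ends about August 2027. The interval from the presurgical scan to the 18-month scan is 18 − 12 = 6 to 18 − 10 = 8 months.

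| Assumed last enrolment | Months left | Projected total | Rate needed for 39 (per month) | Multiple of observed rate |
|---|---|---|---|---|
| End February 2027 (6 months before end August 2027) | 10.8 | 15.2–15.8 | 2.86 | 4.0–4.3 |
| 4 April 2027 | 12.0 | 15.9–16.6 | 2.58 | 3.6–3.9 |
| End June 2027 (6 months before end 2027) | 14.9 | 17.8–18.7 | 2.09 | 2.9–3.2 |
| August 2027 | 15.9–16.9 | 18.5–20.1 | 1.84–1.95 | 2.6–3.0 |
| End 2027 | 20.9 | 21.8–23.0 | 1.48 | 2.1–2.2 |

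The June 2027 row is the latest enrolment that still allows an 18-month visit by the end of 2027. It uses the shortest interval and leaves no time for analysis. The last row ignores follow-up altogether.

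**Sampling error in the rate.** The exact 95% Poisson interval for a count of 8 is 3.45 to 15.76. At the upper limit, the end-2027 total is 8 + (15.76 / 12.1) × 20.9 = 35 to 8 + (15.76 / 11.1) × 20.9 = 38. That exceeds 30 enrolled but is still below 39. This is a limit for the underlying rate; a prediction interval for the final count would be wider.

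**Share of referrals.** So far, 8 of 50 to 60 a year is 13% to 16%. Reaching 39 by the end of 2027 needs 31 / (20.9 / 12) = 17.8 a year, or 30% to 36% of referrals. By the end of February 2027 it needs 31 / (10.8 / 12) = 34.4 a year, or 57% to 69%. The article does not say what share of referrals is eligible.

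**Part 3: which aim is affected**

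Aim 1 relates presurgical anatomy to the procedure performed, so it does not need the 18-month visit. The 30% is not split by visit, so from 39 enrolled aim 1 could keep anywhere from 27 (all loss falls before or at the first scan) to 39 (none does). Aim 2 bears the whole loss. As an illustration with enrolment to mid-2027, it would keep 17.8 × 0.70 = 12.5 to 18.7 × 0.70 = 13.1, about 13 children.

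**The case against.** The strongest reply is that nothing quantitative rests on 30. The size is justified by pilot status, a single site and precedent. No power, precision or effect size is stated, and the Strengths and Limitations section concedes a small sample. So 27 instead of 30 changes no declared operating characteristic. This stands, and it limits the severity. It does not make the sentence correct.

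The second reply is that accrual is openly reported, that a first-year rate from 8 children is a weak basis for extrapolation, and that the referral pool leaves room to speed up. This also stands. A reader might infer that 39 cannot be reached; the article does not support that. A constant rate is an assumption, and by the end of 2027 the target would need about a third of referrals.

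Other stronger readings also go too far:
- One might carry an early-2027 cut-off and the full 30% loss into both aims and conclude that only 10 or 11 children will be evaluable. The Statistical Analysis section includes every child with data at the relevant time point, and Evaluation Outcomes allows imputation, pairwise deletion and cross-sectional analysis. A child who misses the later visit can still count for aim 1.
- One might say that the regression models were designed for 30 children. The article attaches no number to either model.
- One might want a rule that drops hypothesis tests below some number, such as 20 children. Nothing in the article yields such a threshold, and it would change the analysis rather than correct the wording.

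**Conclusion.** The attrition figure is wrong as written. At the plan's own 30%, 39 enrolled gives about 27 retained; 30 retained needs 43 enrolled, or attrition of about 23%. This rests only on reading 30 as the number to be kept, which is the only reading under which the allowance for loss makes sense.

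The reassurance about recruitment does not fit the reported accrual. At a constant rate, total enrolment is below 30 at every deadline examined, and 39 needs roughly 2 to 4 times the observed rate. These figures depend on the constant rate and on the assumed deadline; the February 2027 row is the pessimistic end of the range. This is a feasibility concern, distinct from the arithmetic error and less certain. Of the two it is the larger in children.

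Overall severity is minor to moderate for an exploratory pilot with no stated power.

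**What to change.** 1. Correct the attrition sentence in one of three ways: 39 enrolled with about 27 expected to be retained at 30% attrition; 43 enrolled to retain 30; or 39 enrolled to retain 30 at about 23% attrition, if that is the rate meant.
2. Replace the statement on recruitment capacity with a projection from actual accrual. Show the range by deadline and label both the deadline and the constant rate as assumptions. If faster accrual is expected, say why.
3. Give the expected number of children for aim 1 (presurgical data and procedure) separately from aim 2 (18-month visit needed), with the attrition assumed at each visit.

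The cost is wording. The first and third options need no more children than planned; choosing 43 adds 4 to the target (43 − 39), which makes the accrual gap wider. The expected numbers will look less favourable. Analysis had not begun at the reported date, so the correction can be made without any question of being data-driven.

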### Surgical Considerations

Participants will undergo primary palatoplasty within a typical early palate repair window prior to 15 months [38]. Two standard surgical approaches will be evaluated: IVV and Furlow DOZ. These 2 procedures are commonly used for primary palatoplasty at the study site. Due to the observational nature of this study, no standardization or changes to the surgeons’ procedures will take place; however, individual variability will be accounted for by recording the operating surgeon of each participant and controlling for any significant differences between surgeons in the analysis. Both procedures aim to restore the LVP “sling” to its intended anatomical position in the posterior velum but differ in technique. IVV reorients the muscle bundles end to end without overlap and closes the mucosa with a straight-line suture. DOZ repositions the LVP muscle via opposing Z-shaped incisions, lengthening the velum and creating overlap of the muscle bundles. All surgeries will be performed at a single institution by 1 of 5 operating surgeons. Procedure selection and the use of tissue adjuncts will be determined intraoperatively based on the surgeon’s clinical expertise, which may include a perceptual assessment of the amount of palatal tissue and/or tension upon closure of the cleft defect; no randomization will be performed. Tissue adjuncts, in this context, refer to flaps or grafts added to the palate from an alternate location in the mouth (eg, buccal fat pad flap or buccal myomucosal flap).

### Study Design and Data Collection

As part of the study protocol, MRI scans will be acquired presurgically (approximately 10-12 months depending on surgical timing) and at approximately 18 months of age. These time points were selected to reflect changes in both speech production and anatomy before and after surgery. The first time point, which will occur within 2 weeks prior to the scheduled primary palatoplasty, is relevant for imaging used in presurgical planning. While the timing of the presurgical MRI relative to surgery may vary based on clinical scheduling, all MRI data will be collected solely for research purposes and will not be used to guide surgical decision‑making. Surgeons will not be provided with study MRI findings when determining the surgical approach. At each visit, infants will undergo a nonsedated MRI of the velopharynx using a “feed and wrap” protocol [39], with age- and size-appropriate hearing protection and head stabilization cushions. Fast 2D T2-weighted turbo spin echo scans will be acquired first to minimize motion artifacts, followed by high-resolution 3D anatomical scans covering the oropharyngeal anatomy. MRI datasets will be processed and analyzed using Amira Software (Thermo Fisher Scientific), with custom resampling to visualize the entire LVP muscle from origin to insertion via an oblique-coronal plane. Details on type, location, and timing of data collection are outlined in Figure 1.

**Figure 1 figure1:**
[figure not shown]
Participant-level timeline for multimodal data collection throughout the study. ASQ-3: Ages and Stages Questionnaire, Third Edition; CDI: Communicative Development Inventories; MRI: magnetic resonance imaging.

At both time points, caregivers will also complete an at-home speech recording using a LENA digital language processor (LENA Foundation) worn in a custom vest, along with a structured book reading task to capture 2 to 4 hours of the child’s vocalizations and target words. Audio files will be analyzed using modified naturalistic listening in real time (NLRT) [20,40,41]. Per the NLRT protocol, consonants will be included in the analysis only if they are produced at least twice across the sampled segments. Reflexive vocalizations will be excluded, whereas meaningful productions, including whispered or sung sounds, will be included. The primary outcome measure is consonant inventory size, defined as the total number of distinct consonants meeting the inclusion criterion across the full analyzed sample.

At both time points, caregivers will complete an intake form, the Ages and Stages Questionnaire, Third Edition [42], and the MacArthur-Bates Communicative Development Inventories [43]. Hearing-related data will be taken from the participants’ medical charts from birth up to the 18-month time point to characterize developmental, communicative, and middle-ear status alongside MRI and speech data (see Textbox 1 for a summary of participant data collected at each visit). Hearing data may include tympanometry, otitis media, and newborn hearing screening results, as available. Standardized procedures for MRI acquisition and speech data collection will ensure reliability and minimize the burden on participants and caregivers. These time points are supported by prior research demonstrating that velopharyngeal closure and early speech production are measurable in infants and toddlers with and without cleft palate. Specifically, velopharyngeal closure is largely complete by 19 months [34], some children with repaired cleft palate achieve consistent closure for stop consonants by 14 months [35], and modified NLRT provides reliable assessment of early consonant production as early as 16 months [40].

Participant data collected after enrollment and updated for each visit.

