**Methods:**

A total of 30 infants with cleft palate will be recruited prior to palate repair. Within 2 weeks of repair, participants will undergo nonsedated magnetic resonance imaging (MRI) of the velopharynx and produce a home-based speech recording. Participants will complete the same protocol after palate repair at 18 months of age. Data will be analyzed by independent raters following completion of a training protocol. Anatomical dimensions of the velopharynx will be extracted from the MRI scans. The number and diversity of oral stop consonants will be extracted from the speech recordings. Interrater and intrarater reliability will be assessed. Logistic regression will be used to evaluate which presurgical anatomical measurements are predictive of surgical procedure selection. Analysis of covariance will be used to examine whether postsurgical anatomical measurements are associated with diversity of oral stop consonant production.

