### Aims of This Study

In summary, recent studies quantifying the velopharynx in children have generally examined anatomy and physiology in isolation [35], and many have relied on cross-sectional designs [15,32]. Few have tracked both anatomical and functional measures at 2 time points within the same individual. Multidimensional data before and after palatoplasty are crucial for understanding how palate repair influences both velopharyngeal structure and function. These individualized assessments are key for translating basic science findings into patient-specific surgical planning and targeted interventions. This protocol aims to take an essential step toward precision medicine in infants with cleft palate.

This study combines nonsedated MRI–based anatomical assessment with functional speech measurements in the same infants before and after palatoplasty. By linking patient-specific anatomy before and after palate repair to early speech outcomes, we aim to establish data-driven criteria for individualized surgical planning and targeted speech monitoring. This approach addresses a critical gap by providing quantitative, objective measures of surgical success and velopharyngeal development, moving beyond subjective assessment. Ultimately, these findings may lead to work that reduces persistent speech deficits, prevents multiple surgeries, and lessens the associated psychosocial and financial burden of cleft palate. Specifically, this study has two primary aims:

To establish which presurgical anatomical variables are predictive of surgical procedure selection based on perceptual assessment of intraoperative tension for palate repair (hypothesis: preoperative cleft width and LVP muscle length are predictive of surgical procedure selection based on intraoperative tension of palatal tissue)To determine which postsurgical anatomical features are associated with the greatest diversity in oral stop consonant production at 18 months in children with repaired cleft palate (hypothesis: a longer velum, greater effective velopharyngeal ratio, and continuity of the LVP muscle are associated with greater diversity of oral stop consonants by 18 months but not with procedure type)

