### Evaluation Outcomes

The primary outcomes correspond to the 2 study aims. For aim 1, the primary outcome is the type of surgical procedure performed (IVV or DOZ with or without adjunct tissue use) predicted by preoperative anatomical variables, namely, cleft width and LVP muscle length. For aim 2, the primary outcome is the diversity of oral stop consonants produced at 18 months, serving as a functional measure of velopharyngeal competence. Secondary outcomes include additional anatomical measures (effective velar length, effective velopharyngeal ratio, and LVP muscle continuity) and developmental and language scores. Anatomical variable definitions are outlined in Table 1. Exploratory tertiary outcomes will examine modifiers of anatomy and speech, including sex, demographic characteristics, tympanometry results, and other developmental assessments. Missing data will be imputed (when appropriate) or addressed using pairwise deletion. Additionally, data may be analyzed cross-sectionally to meet the study aims.

**Table 1 table1:** Anatomical variables and corresponding definitions as obtained from magnetic resonance imaging for aims 1 and 2.

Variable	Definition
Cleft width	Distance between the lateral margins of the cleft at the widest point
Effective VP^a^ ratio	Effective velar length/pharyngeal depth
Effective velar length	Length of the velum from the posterior hard palate to the LVP^b^ muscle
LVP muscle angle of origin	Interior angle created by the lines drawn to measure distance between the origin points and LVP muscle length
LVP muscle continuity	Whether the LVP muscle is continuous through the midline (yes or no)
LVP muscle length	Length of the LVP muscle along one side from origin to insertion
Origin-origin distance	Distance between the points of origin of the LVP muscle
Pharyngeal depth	Distance from the posterior hard palate to the posterior pharyngeal wall at the palatal plane
VP ratio	Total velar length/pharyngeal depth
Velar insertion distance	Distance between the locations where the bilateral LVP muscle bundles insert into the body of the velum (ie, repaired velar width)
Velar length	Length of the velum from the posterior hard palate to the tip of the uvula
Velar thickness	Distance from the velar knee to the velar dimple

^a^VP: velopharyngeal.

^b^LVP: levator veli palatini.

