### Statistical Analysis

All participants with data at the relevant time points will be included in each analysis. The primary outcome will be evaluated using binomial logistic regression to determine how preoperative anatomical variables predict surgical procedure selection, controlling for sex, race, and cleft type. Principal component analysis may be applied to reduce dimensionality among anatomical predictors. The secondary outcome will be assessed using a 2-way analysis of covariance examining the effects of surgical type and number of oral stops on postsurgical anatomical measures, controlling for sex, cleft type, and developmental and language scores.

To ensure scientific rigor, intrarater and interrater reliability will be calculated for both MRI and speech measures. Independent raters will measure MRI scans and consonant productions following completion of a structured reliability training protocol to enhance measurement accuracy and precision. This training will consist of a guided review of the velopharyngeal MRI and speech literature, a detailed study of relevant cleft MRI anatomy and speech characteristics, and repeated practice measurements of both typical children and those with cleft palate until a predetermined level of agreement is reached. Each measurement training cycle will be followed by discussion-based debriefing and troubleshooting. The primary rater will measure all samples, whereas a second rater will measure a randomly selected 10% of the samples to calculate interrater reliability. The primary rater will rerate a random selection of 10% of the samples to calculate intrarater reliability.

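### Two different speech variables are each labelled the primary outcome, and the Aim 2 analysis models neither of them as an outcome

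*Protocol article*

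**What the plan says.** The relevant statements stand in several sections of the protocol article.

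- **Study Design and Data Collection**, in the paragraph on home recordings after Figure 1: "The primary outcome measure is consonant inventory size, defined as the total number of distinct consonants meeting the inclusion criterion". The inclusion criterion is production at least twice across the sampled segments. The paragraph covers recordings at both visits, and the sentence names neither an aim nor an age.
- **Evaluation Outcomes**: "The primary outcomes correspond to the 2 study aims", and then "For aim 2, the primary outcome is the diversity of oral stop consonants produced at 18 months". The section gives the reason for this choice, which is that oral stops serve as a functional measure of velopharyngeal competence. Consonant inventory size appears in neither its secondary nor its tertiary list.
- **Aims of This Study**: "Specifically, this study has two primary aims". The second concerns diversity of oral stops at 18 months. The Abstract (Objective and Methods) and the Discussion (Expected Findings) use the same construct.
- **Statistical Analysis**: "The primary outcome will be evaluated using binomial logistic regression to determine how preoperative anatomical variables predict surgical procedure selection". The next analysis is introduced with "The secondary outcome will be assessed using a 2-way analysis of covariance" and is described as "examining the effects of surgical type and number of oral stops on postsurgical anatomical measures". The Abstract's Methods paragraph ties the analysis of covariance to oral stop diversity, so this is the Aim 2 analysis.

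**The concern.** A primary outcome should be one variable, at one time, with one analysis. Here two sections of the Methods give the primary label to different variables, and no sentence ranks or links them. The analysis section then does not treat the Aim 2 variable as an outcome.

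The difference is one of substance. A total consonant inventory can be well above zero in a child who produces no oral stops, because it also counts nasals, glides and other consonants. Such a child would score at the bottom on the measure chosen to reflect velopharyngeal competence and could score respectably on the other.

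At stake is the freedom to decide, after seeing the data, which variable carries the Aim 2 conclusion. The Discussion expects the work to yield preliminary criteria for surgical planning and speech monitoring, so the choice has consequences even in a pilot.

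**Working it through.** **Step 1. The two definitions side by side.**

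| | Study Design and Data Collection | Evaluation Outcomes |
|---|---|---|
| Label | primary outcome measure | Aim 2 primary outcome |
| Variable | all distinct consonants meeting the criterion | diversity of oral stops |
| Range | not limited to six | 0 to 6 (the Background refers to six stop consonants) |
| Age | none named; recordings at both visits | 18 months |
| Link to velopharyngeal competence | none stated | stated as the reason for the choice |

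The variables differ in content, range and timing, so they cannot be two names for one quantity.

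**Step 2. The analysis section against the outcomes section.** The Aims and Evaluation Outcomes sections give two primary aims with one primary outcome each. The Statistical Analysis section has one primary outcome, procedure selection, which belongs to Aim 1. The label on the analysis of covariance can be read in two ways:

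- The secondary outcome is oral stop production. The Aim 2 primary outcome has then been demoted.
- The secondary outcome is the anatomical measures. Evaluation Outcomes lists several of these as secondary, and they are the dependent variable of the model as written. The label then fits, but the Aim 2 primary outcome appears only as a factor.

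On either reading the model puts oral stops on the predictor side, so no stated analysis has the Aim 2 primary outcome as its dependent variable.

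**Step 3. Size of the freedom to choose.** The article states no significance level, power or correlation, so there is no figure of its own to reproduce. Assumptions: a two-sided 5% level (critical value 1.96), two candidate speech outcomes tested against one anatomical feature, no true association, and test statistics that are bivariate standard normal with correlation r.

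P(at least one significant) = 1 − P(|Z1| ≤ 1.96 and |Z2| ≤ 1.96)

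| r | P(at least one p<0.05) |
|---|---|
| 0.5 | 9.1% |
| 0.6 | 8.8% |
| 0.7 | 8.3% |

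The ceiling is r = 0, where 1 − 0.95² = 9.75%; the floor is 5%, when the two variables are perfectly correlated. The range 0.5 to 0.7 is an assumption, and the result changes little across it.

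**The case against.** The strongest reply is that the endpoint is not really in doubt. The section whose purpose is to define outcomes fixes it by aim, variable and age, and the Abstract, Aims and Discussion agree. The conflicting sentence closes a paragraph on speech coding and may mean only the main output of that coding. Most of this stands: the weight of the text favours oral stop diversity, and a reader who infers that the article leaves Aim 2 with no identifiable primary endpoint goes too far. What remains is that the sentence uses the primary label without that qualification, and nothing elsewhere withdraws it.

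Two further inferences are tempting and are not supported.

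- *Three candidate outcomes.* The Abstract says "The number and diversity of oral stop consonants will be extracted from the speech recordings", which might suggest that number and diversity are separate quantities. But the coding rule yields a count of distinct consonants, and the Background also counts different stops. The number of oral stops in the analysis section can therefore simply be diversity. Only two candidates are firmly established, and an error rate computed for three would overstate the problem.
- *The analysis section expressly demotes oral stop diversity.* It does not say so. The secondary label may belong to the anatomical measures, as Step 2 shows.

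It can also be said that this is an exploratory pilot that claims no error rate. That is a fair reason not to lean on the 8 to 9%. It does not excuse naming two primary variables. Nor is this detail that an article leaves to a fuller document: the statements present in the Methods conflict.

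**Conclusion.** The concern holds in limited form. One sentence gives the primary label to total consonant inventory size, against several consistent statements that the Aim 2 primary outcome is oral stop diversity at 18 months. The analysis section compounds this: its labels do not match the two primary aims, and the primary speech outcome enters as a factor and never as an outcome. These are internal contradictions, and they rest on the text alone.

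The numerical consequence is modest and conditional: about 8 to 9% instead of 5% per anatomical feature, with two candidates, an assumed 5% level and an assumed correlation of 0.5 to 0.7. The finding does not depend on that figure.

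**What to change.** 1. State once, and use throughout: the Aim 2 primary outcome is the number of different oral stops (0 to 6), each produced at least twice in the analysed sample, at 18 months.
2. In Study Design and Data Collection, relabel total consonant inventory size as a secondary or descriptive speech measure.
3. In Statistical Analysis, call this the Aim 2 primary analysis, use the same variable name, and make oral stop diversity the dependent variable, with postsurgical anatomy and surgical type as predictors. Changing the label alone would not be enough, because the primary outcome would still be a factor in a model of anatomy. Reversing the model also suits LVP muscle continuity, which Table 1 defines as yes or no and which works more naturally as a predictor than as a dependent variable in an analysis of covariance.

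The cost is rewording in the two Methods sections and respecifying one model. No new data are needed. Eight participants had been enrolled by April 4, 2026 and analysis had not begun, so the outcome can still be fixed ahead of any results. The article already undertakes to publish protocol modifications with the findings.
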